#### Survival

The survival of the two treatments will be analysed at 12 months. Survival is the success of the treatment, indicated by the absence of additional surgery during the study period due to insufficient improvement or symptom recurrence. If a participant is scheduled for additional surgery, the date of enrolment on the waiting list for surgery is recorded, and survival, measured in months, will be calculated from the initiation of study treatment to that date.

#### Adherence to the exercise therapy program

To assess adherence, participants in the exercise therapy group will report the number of completed exercise sessions during the 12-week intervention period. After 12 weeks, they will also be asked to rate their experience with the exercise therapy program on an 11-point self-report Likert scale with the single question “How have you experienced the training program for your wrist?”, ranging from −5 to +5, where “−5” indicates “very difficult” and “ +5” signifies “very easy”.

### Participant timeline {13}

An overview of the trial design can be found in the flowchart (Fig. 1). The enrolment, intervention schedule, and outcome measures are illustrated in the SPIRIT diagram (Fig. 2).

### Sample size {14}

The reported minimal clinically important difference (MCID) of PRWE is 14 points (out of 100) based on previous research [41]. To show a difference of at least 14 points in PRWE score between partial wrist denervation and the education and exercise therapy program (SD 24) [13], after 6 months, 64 participants are required in each treatment arm. The power will be 80% (*p* < 0.05). To account for lost to follow-up, we aim to include 140 participants in total, 70 per treatment arm.

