## Statistical methods

### Statistical methods for primary and secondary outcomes {20a}

For descriptive analysis, categorical data is presented as frequencies and percentages, whereas ordinal or skewed data is presented as median (IQR) and normally distributed continuous variables as mean (SD). For the primary endpoint, comparison between partial wrist denervation, and the patient education and exercise therapy program, the Wilcoxon signed-rank test will be used for paired data, and the Mann–Whitney *U*-test will be applied for unpaired data when the data are non-normally distributed or ordinal.

*T*-tests will be employed for changes in continuous data that follow a normal distribution, while the chi-square test will be used for categorical data. Normality will be assessed by the Shapiro–Wilk test. Generalized estimating equations (GEE), adjusted for age, sex, pain catastrophizing, operated dominant hand, SLAC/SNAC OA classification according to Watson and Vender [3, 4], and treatment site (Stockholm or Malmö), will be used for analysis of differences between groups regarding longitudinal data with repeated measurements. A robust estimator covariances matrix will be used. The working correlation matrix is selected according to the lowest Quasi-likelihood under Independence Model Criterion (QICC), and linear models will be used for all variables. Kaplan–Meier analysis will be performed to generate survival curves and Cox regression to compare differences in survival at 12-month post-intervention. *P*-values < 0.05 are considered significant.

Statistical analyses will be conducted following the intention-to-treat (ITT) principle. A secondary per-protocol (PP) analysis will be performed as a sensitivity analysis to assess the robustness of the findings. If a participant requires additional wrist surgery during follow-up or has a major trauma or other disease affecting the included hand, analyses will be conducted according to ITT up to that event. Data collected after such an event will not be analysed.

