### Interim analyses and stopping guidelines{21b}

Interim analyses will be performed by an independent statistician after the inclusion of 50 and 100 participants to determine whether the power calculation requires adjustment due to variance differing from initial expectations. No stopping guidelines have been established, as partial wrist denervation is a well-established treatment with a low complication rate [42]. Additionally, patient education and exercise therapy are recommended treatments for OA with minimal risk of adverse events [22].

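### The sample-size inputs and result cannot all be true: 14 points, SD 24, 5% and 80% power give 48 per arm, not 64

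*Protocol article*

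**What the plan says.** The Sample size section of the protocol article takes 14 points as the minimal clinically important difference on the PRWE and builds the calculation on it: "To show a difference of at least 14 points in PRWE score between partial wrist denervation and the education and exercise therapy program". The SD is 24, taken from a cited study. The result reads "after 6 months, 64 participants are required in each treatment arm. The power will be 80" per cent, at p < 0.05. Loss to follow-up is handled afterwards, by raising the target to 70 per arm and 140 in total.

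The Statistical methods section sets the significance threshold (P-values "< 0.05 are considered significant") and allows a t-test or, for non-normal or ordinal data, a Mann-Whitney test. The Sequence generation section gives 1:1 allocation. The section on interim analyses plans a look after 50 and after 100 participants "to determine whether the power calculation requires adjustment due to variance differing from initial expectations".

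**The concern.** Difference, SD, significance level, power and n per arm are all printed, so the calculation can be checked directly. The standardised effect is 14/24 = 0.583. Sixty-four per arm is the familiar answer for a standardised effect of 0.50 at 80% power. At least one printed figure therefore appears to be wrong.

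Two things are at stake. First, the power the trial reports for its primary comparison may not be the power it has. Second, the interim looks compare the observed variance with what was expected and ask whether the power calculation needs adjusting. If the printed SD and the printed n imply different variances, the statistician doing that check has no single reference to work from.

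**Working it through.** **Inputs.** Difference 14, SD 24, power 80% and p < 0.05 (Sample size section); 1:1 allocation (Sequence generation); t-test or Mann-Whitney test (Statistical methods). Sidedness is not stated. I take two-sided as the default and also try one-sided.

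**Attempt to reproduce 64.**

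- Normal approximation: n per arm = 2(z₀.₉₇₅ + z₀.₈₀)²(SD/difference)² = 2(1.96 + 0.8416)²(24/14)² = 46.1, so 47.
- Two-sample t-test (noncentral t), d = 0.5833: 47.1, so 48.
- Mann-Whitney test, efficiency 0.955: 47.11/0.955 = 49.3, so 50.
- Mann-Whitney test, worst-case efficiency 0.864: 47.11/0.864 = 54.5, so 55. A flat 15% inflation also gives 55.
- One-sided 5%: 37 (normal) or 38 (t).

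None of these gives 64.

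**Could loss to follow-up explain it?** Going from 48 to 64 would need a loss of 1 − 48/64 = 25%. The protocol applies its allowance after the 64, from 64 to 70, which is 1 − 64/70 = 8.6%. No multiplicity adjustment or design effect is stated either.

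**Power at the stated sizes, with 14 points, SD 24 and two-sided 5%.**

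| n per arm | Normal approximation | t-test |
|---|---|---|
| 48 | 81.5% | 80.7% |
| 64 | 91.0% | 90.6% |
| 70 | 93.2% | 92.9% |

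**What would produce 64?** Each of these changes one stated input:

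- Power 90% instead of 80%: 62 (normal) or 63 (t, from 62.7).
- SD 28 instead of 24, so d = 14/28 = 0.50: 63 (normal) or 64 (t).
- Difference 12 instead of 14, so d = 12/24 = 0.50: 63 (normal).

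Solving the t-test at 64 per arm and 80% power gives d = 0.499. That is an SD of 14/0.499 ≈ 28.05 for 14 points, or a difference of 0.499 × 24 ≈ 11.98 at SD 24. The 12-point route sits badly with the protocol, which names 14 as both the minimal important difference and the target. The two main readings are therefore SD 24 with about 90% power, or SD about 28 with 80% power.

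**Power for 14 points if the SD is 28.** By t-test, 80.1% at 64 per arm and 83.6% at 70 per arm.

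**The interim reference.** The printed SD says that the expected variance is 24² = 576. The printed n and power say that it is about 28² = 784. The ratio is 784/576 = 1.36, so a check against one starts 36% away from a check against the other.

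**The case against.** The best defence is that the plan is safe either way. With SD 24, 64 per arm gives 90.6% power for 14 points; with SD 28 it gives 80.1%. The target of 140, the primary comparison and the significance level need not change. That stands, and it limits the weight of the point.

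A second defence is that 64 may have been computed correctly from an SD that was not printed. If 24 is the SD of a single score and the calculation used the change from baseline, the change SD is 24√(2(1 − ρ)). This equals 28 when ρ = 1 − (28/24)²/2 = 0.32. It is arithmetically possible, and the primary outcome is indeed a change. But the text does not say which SD it quotes and gives no correlation, so this does not rescue the statement as printed.

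A reader might infer three stronger things that the document does not support:

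- **That the trial recruits 16 per arm too many, or that the power figure is the wrong one.** Both are true only if 14 points and SD 24 are right. The source of the SD is not at hand, and if the SD was 28, both 64 and 80% are correct.
- **That the interim looks will over-recruit by scaling 64 by a variance ratio, or will cut the trial to 48 per arm.** The interim section describes neither a scaling rule nor a reduction.
- **That the allowance for loss is wrong, because 70 per arm would tolerate about 31% loss (1 − 48/70).** That again depends on SD 24; the 8.6% step from 64 to 70 is the same however 64 was reached.

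**Conclusion.** The point holds as an internal inconsistency: 14 points, SD 24, two-sided 5%, 80% power and 64 per arm cannot all be true. The printed inputs give 48 per arm by t-test and at most 55 with the worst-case Mann-Whitney allowance. Either the power at 64 is about 90.6%, some 11 percentage points above the stated figure, or the SD behind the calculation was about 28, some 4 points above the stated one. The document does not show which.

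This rests on a two-sided test, which the protocol does not state; a one-sided test moves the answer further from 64. It does not show an underpowered trial, since both main readings give at least 80% power for 14 points at 64 per arm. The practical consequence is confined to the reported power and to the reference for the two interim variance checks. It should be fixed, but it does not threaten the design.

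**What to change.** Keep 140 participants and reconcile the Sample size section in one of two ways, according to what the sponsor's original calculation shows:

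1. If 14 points and SD 24 were intended, state that 64 per arm gives about 90% power with a two-sided 5% test, and that 48 per arm would give 80%.
2. If 80% power was intended, print the SD that produced 64 (about 28 for 14 points) and say whether it is the SD of the 6-month score or of the change.

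Then add a sentence to the interim section saying that the check uses the corrected inputs as its reference: difference 14, the corrected SD and the corrected power. Recruitment began in March 2024, so this should be done before any interim look still to come.

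The cost is a few sentences in the protocol, with the same wording carried into any other trial document that repeats the calculation. No patients are added and no analysis changes.

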### Recruitment {15}

All eligible patients diagnosed with painful SLAC or SNAC OA at the Departments of Hand Surgery at Södersjukhuset and Skåne University Hospital will be invited to participate in the study.

## Assignment of interventions: allocation

### Sequence generation {16a}

Participants will be randomly assigned to either partial wrist denervation (intervention group) or patient education and exercise therapy (control group) with a 1:1 allocation. Sealed and unnumbered envelopes with a fixed block size of 10, with 5 envelopes per arm, will be used. The block sizes will be disclosed to the dedicated research nurse, who is blinded to the treatment allocations and randomly assigns the envelopes. The randomization will not be stratified.

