### Concealment mechanism {16b}

Opaque, sealed envelopes stored in a locked safe, accessible only to the researchers responsible for the trial, will ensure allocation concealment. The sealed envelopes will be opened exclusively by the hand surgeon during the enrolment process.

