### Implementation {16c}

After obtaining signed informed consent, the dedicated research nurse assigns the randomized envelope to the treating hand surgeon, who is responsible for enrolment and intervention allocation. Participants assigned to surgery are placed on the surgical waiting list by the treating hand surgeon. While the enrolling hand surgeon may perform the procedure, they will have no further contact with the participant to maintain allocation concealment. For participants assigned to patient education and exercise therapy, the hand surgeon will notify the PTs involved in the research study. The designated PTs will then contact the participant to schedule an appointment for the exercise therapy program at the clinic.

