PRWE is chosen as the primary outcome since it is a valid and reliable outcome for wrist OA [33] that evaluates both function and pain and focuses on the patient’s perspective [31]. However, PROMs are inherently subjective and may be influenced by age, expectations, socioeconomic status, and psychological factors [46, 47]. To account for this, grip strength and range of wrist motion are included as objective secondary outcomes. Additionally, pain catastrophizing is incorporated as a covariate in the GEE model to adjust for psychological influences on outcomes.

The prevalence of wrist OA is relatively low compared to OA in other joints [48, 49]. By adopting a multicentre design involving two major hand surgery departments in Sweden, this trial has the capacity to recruit a sufficient sample within a reasonable time frame, ensuring statistical power and robust results. Another strength is the focus on two common types of wrist OA, SLAC and SNAC, rather than including a heterogenous group of OA types. This increases internal validity, as treatment outcomes may differ among various OA subtypes.

A potential challenge is treatment adherence in the exercise therapy group. Exercise-based interventions require adherence to the program over weeks or months to achieve benefits, which may be difficult for some individuals [50]. Since pain relief from exercise therapy may take 6–8 weeks [51], maintaining participant engagement is critical. To monitor and evaluate adherence, an exercise diary will be used.

A limitation is the lack of participant blinding due to the nature of the interventions. This introduces a risk of performance bias and detection bias, particularly for subjective outcomes [52]. To strengthen the study design, objective outcomes such as ROM and grip strength are included as secondary outcome measures. Assessors and data analysts will be blinded to minimize bias.

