### Trial status

This protocol is version 2.0 (19th February 2025). Any future protocol amendments that may impact the study’s conduct or ethics require approval from the ethical review board. Recruitment of participants began in March 2024 and is estimated to be completed in 2027.

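### Unnumbered envelopes in a fixed, published block of 10, opened by the surgeon who enrols, let late-block allocations be inferred and make a substitution harder to detect

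*Protocol article*

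**What the plan says.** Sequence generation {16a} sets the method: "Sealed and unnumbered envelopes with a fixed block size of 10, with 5 envelopes per arm, will be used". It continues: "The block sizes will be disclosed to the dedicated research nurse, who is blinded to the treatment allocations and randomly assigns the envelopes". On strata it says: "The randomization will not be stratified".

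Concealment mechanism {16b} gives the safeguards: "Opaque, sealed envelopes stored in a locked safe, accessible only to the researchers responsible for the trial, will ensure allocation concealment". It also says who opens the envelope: "The sealed envelopes will be opened exclusively by the hand surgeon during the enrolment process".

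Implementation {16c} places the hand-over after signed consent, when "the dedicated research nurse assigns the randomized envelope to the treating hand surgeon, who is responsible for enrolment and intervention allocation".

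The Discussion acknowledges that the trial is open to participants: "A limitation is the lack of participant blinding due to the nature of the interventions". The article is dated 30 October 2025, and Trial status says: "Recruitment of participants began in March 2024 and is estimated to be completed in 2027".

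**The concern.** Three stated features combine.

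- **The recruiter sees allocations.** The surgeon who enrols also opens the envelope, so past allocations are known to a person who decides when, and whether, to approach the next patient.
- **The block is fixed and public.** The section on sequence generation describes the block size as something told to the research nurse. Since publication anyone can know it, including surgeons still recruiting. As a block runs down, the arm with fewer openings so far becomes the likelier next one, and the last envelope is always known.
- **The envelopes carry no number.** No envelope is tied to a position in a sequence, so an exchange or a discard and re-draw within a block does not show up as a break in order.

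At stake is selection bias. A surgeon who expects one arm could delay or withhold an approach to a particular patient, and the groups would then differ at baseline in ways that covariate adjustment may not remove. The primary outcome is self-reported by unblinded participants, so concealment before allocation is one of the few protections the design has.

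**Working it through.** **Plan's own figures.** The article gives no predictability figure. Its numbers fit together: 140 participants in blocks of 10 make 140/10 = 14 blocks, and 14 × 5 = 70 per arm, as Sample size {14} states.

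**Inputs.** Block of 2m = 10 with m = 5 per arm (Sequence generation {16a}), and total 140 (Sample size {14}). A random draw from the envelopes left in a block is equivalent to a randomly permuted block.

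**Ceiling case: an observer who sees every opening and knows where each block starts.**

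1. The allocation made with k envelopes left is certain when all k belong to one arm. The probability is 2·C(10−k, 5−k)/C(10, 5) for k ≥ 2, with C(10, 5) = 252, and it is 1 for k = 1:
   - k = 1: 1
   - k = 2: 2 × 56/252 = 0.444
   - k = 3: 2 × 21/252 = 0.167
   - k = 4: 2 × 6/252 = 0.048
   - k = 5: 2 × 1/252 = 0.008
2. These sum to 1.67 per block, which agrees with 2m/(m+1) = 10/6. That is 16.7%, or 14 × 1.67 ≈ 23 of 140 if it applied to the whole trial.
3. If the observer always names the arm with more envelopes left, the expected number of correct guesses per block is m + (2^(2m)/C(2m, m) − 1)/2 = 5 + (1024/252 − 1)/2 = 6.53. That is 65.3%, or about 91 of 140 against 70 by chance.

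**Shared-list case.** The article does not say whether the two departments draw from one set of envelopes or two. Assume one shared list, a 50:50 split between sites, and a surgeon who sees only the own site's openings but knows the block starts. By simulation, naming the arm that lags at that site is right about 57% of the time.

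**Effect of publication.** Only participants randomised after 30 October 2025 can be affected. The article does not give their number. The ceiling for them is one sixth of however many remain.

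**What different blocks would do.** Same observer, block size known:

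| Block size | Certain in advance | Guessed correctly |
|---|---|---|
| 4 | 33.3% | 70.8% |
| 6 | 25.0% | 68.3% |
| 8 | 20.0% | 66.6% |
| 10 | 16.7% | 65.3% |

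For sizes 4, 6 and 8 mixed at random and undisclosed, simply naming the lagging arm is right about 68% of the time. Varying sizes therefore do not lower the simple guess rate. They remove certainty about where a block ends, and only if the sizes stay hidden.

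**Site strata.** With one unstratified list and about 70 participants at a site, simulation gives a mean absolute arm difference of about 4.7 within that site and a 95th percentile of 12. About 11% of trials reach a difference of 10 or more. This concerns balance, not concealment.

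**The case against.** The stated safeguards are substantial. The envelopes are opaque, sealed and locked away with restricted access. A separate nurse who does not know the contents makes the draw. The surgeon receives the envelope only after consent is signed, and Recruitment {15} says all eligible patients will be invited. Together these make it hard to read, skip or exchange an envelope. They do not affect inference from earlier openings, which works before consent is sought.

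Four stronger readings are tempting and are not supported.

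- **That missing site strata make allocations guessable.** The effect runs the other way: a list shared by two sites is harder to predict (about 57%) than blocks held separately at each site (up to 65%). Adjusting for site in the generalized estimating equations without stratifying on it is a legitimate choice.
- **That the allocation cannot be audited.** Dates of consent, surgical listing and physiotherapy referral can be checked, and so can the 5:5 count in each completed block. The article's silence on an opening log is not evidence that none is kept. The count is a weaker check than it looks, because participants who withdraw before the intervention are replaced (section {18b}).
- **That any enrolling surgeon could guess 65%.** That needs one person who sees every opening and knows the block starts. The article describes consulting surgeons at two departments.
- **That publication exposes the whole trial.** Recruitment began in March 2024, and the only disclosure of block size described before the article is to the nurse.

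It also stands that smaller varying blocks do not improve the guess rate, so the change cannot be justified on that ground.

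**Conclusion.** The point holds in a limited form. Followed as written, the plan leaves a route to selection bias that its safeguards do not close: a recruiting surgeon who sees past allocations can infer late-block ones from a fixed, public block size. The lack of numbers makes an exchange within a block harder to detect.

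The size is at most 1.67 of 10 allocations certain and 65% guessable, for an observer who sees every opening and knows the block starts. It is about 57% for a surgeon who sees one of two equal sites on a shared list. Both rest on a new block starting only when the previous 10 envelopes are used up, and the 57% also on the assumed 50:50 split. Nothing in the article shows that any surgeon has used this route. It is an inexpensive improvement worth making while recruitment is open, not a flaw that invalidates the participants already randomised.

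**What to change.** For all remaining participants:

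- Prepare allocations from a computer-generated list with randomly varying block sizes. Keep the sizes out of the amendment text and any public record until recruitment closes. The gain is loss of certainty about block ends, not a lower simple guess rate.
- Number the opaque envelopes sequentially, open them strictly in order, and write the participant ID on each before opening. Keep a log of date, number, ID and opener. Central release after consent and baseline entry does the same job if a system is already available.
- Site stratification is optional and serves balance within site only. If it is added, pair it with the undisclosed varying blocks, because separate fixed blocks per site would raise predictability.
- Keep all existing allocations, state in the amendment what happens to any part-used block, and report the two randomisation phases.

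The cost is a short amendment and a new set of envelopes or a standard randomisation module, with no extra participants or visits. The downside is having two phases to describe in the report.
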